### Sample size

For both the AM RCT and SC RCT, conventional power (1-beta = .80) and levels of statistical significance (alpha = .05) are chosen. For both trials, the primary outcome data is collected at 6 months post-randomisation.

For the AM RCT, the primary outcome variable is based on the 7-day TLFB alcohol measurement, 6 months post-randomisation. Based on the average of 2 previous RCTs on very similar self-help interventions in the Netherlands versus a control condition (see Riper 2008 and Blankers 2011 in [25]), a Cohen’s d effect size of d = 0.40 is expected. Using the power calculation package “pwr” [41] for R 3.0.1 [41], d = .40 translates into a minimum net sample size of 2 × 99 participants in case of 2-sided testing, or 2 X 78 participants in case of 1-sided testing. Assuming a maximum of 25% non-response at 6 months follow-up, we intend to include 99 × 2 x (100/(100–25)) = 264 (or 208 for 1-sided testing) participants in the alcohol RCT. In case the drop-out rate is lower than 25%, power will be somewhat higher than we anticipate in this calculation, i.e. in that case we are more likely to find a true effect.

For the SC RCT, the primary outcome variable is based on the 7-day TLFB smoking measurement: self-reported abstinence in the last 7 days prior to the primary measurement point, 6 months post-randomisation. Based on a study by Duffy et al. amongst cancer survivors [12], a quit-rate of 30% in the active smoking cessation intervention group, vs 15% in the smoking cessation control group can be expected. This translates into a relative risk (RR) of 2.14, which is comparable to the RR estimate in a recent Cochrane review (RR = 2.05) [26]. Based on a pilot trial of an ACT smoking cessation internet intervention [42], a 23% quit rate in the experimental arm vs a 10% quit rate in the control arm can be expected (RR = 2.20), at the 3 months follow-up. Based on the average of these RRs, a RR = 2.1 is expected. This translates into a 21% quit rate in the experimental condition, assuming a 10% quit rate in the control condition at 6 months post-randomisation. Using “pwr” [43] for R 3.0.1 [41], a 21% quit-rate vs 10% quit-rate translates into a net sample size of 2 × 157 participants, based on 2-sided tests (2 X 124 for 1-sided tests). Assuming 25% non-response at 6 months follow-up, we need 157 × 2 x (100/(100–25)) = 419 participants in the SC RCT for 2-sided tests, and 331 for 1-sided tests).

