The described power analyses are conservative. We may perform half-way post-hoc power analyses for both RCTs, based on those we will evaluate our assumptions underlying these power calculations and may adjust the sample sizes if necessary. We might for example not fully compensate the expected 25% drop-out, as drop-out rates might be lower and we will perform intention-to-treat analyses including multiple imputation, which partially recovers power. One-sided testing is mentioned because it is very plausible that the interventions will have a positive effect on SC and AM [25, 26, 42]. Furthermore, within the above mentioned calculation, clustering of measurements (baseline, 3-, 6- and 12-months) within participants and related covariance has not been taken into consideration. Accounting for this could also change required sample sizes.

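### Each trial has a two-sided and a one-sided 5% sample size; the two-sided one leads, but nothing closes the one-sided option or fixes the sidedness of the primary test

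*Protocol article*

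**What the plan says.** The Sample size section of the protocol article opens with one error rate and one power for both trials, and attaches no side to the error rate: "conventional power (1-beta = .80) and levels of statistical significance (alpha = .05) are chosen".

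For AM, "a Cohen’s d effect size of d = 0.40 is expected", which is said to give "a minimum net sample size of 2 × 99 participants in case of 2-sided testing, or 2 X 78 participants in case of 1-sided testing". After allowing for 25% non-response, the recruitment figure is "264 (or 208 for 1-sided testing) participants in the alcohol RCT".

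For SC, quit rates of 21% and 10% are said to give 157 per arm two-sided or 124 per arm one-sided. The recruitment figures are 419 for two-sided tests "and 331 for 1-sided tests".

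The closing paragraph of the same section neither adopts nor rejects the one-sided test. It says only: "One-sided testing is mentioned because it is very plausible that the interventions will have a positive effect on SC and AM". That paragraph also allows a half-way power review, after which the sample sizes may be changed.

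Aims and hypotheses words the effectiveness hypotheses directionally (more reduction, higher quit rate). Statistical analyses names the model family and gives neither a side nor a significance level for the primary comparison.

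**The concern.** Sidedness decides what counts as a positive primary result, and here it also decides how many people are recruited. The document offers two answers to each question and does not choose.

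The reason given for the one-sided option does not support it. Expecting benefit is the normal position before a trial and does not make a one-sided test at the full .05 appropriate. The Background is itself cautious: it describes small effect sizes, mixed results for internet-based smoking cessation, and an alcohol effect that is not sustained after 12 months.

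Two things are at stake. The first is the chance of a false claim of benefit, which doubles under the one-sided option. The second is power, if the smaller size were recruited and the result then judged by a two-sided test.

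**Working it through.** **Inputs, all from the protocol article.** Power 0.80; alpha .05; AM d = 0.40; SC 21% vs 10%; 25% non-response, applied by dividing by 0.75 (Sample size); 1:1 allocation (Randomisation).

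**1. Reproducing the AM sizes.** A two-sample t test with d = 0.40 and 80% power needs 99.08 per arm two-sided and 77.97 one-sided, which agrees with 99 and 78. Inflation: 198/0.75 = 264 and 156/0.75 = 208. All AM figures reproduce.

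**2. Reproducing the SC sizes.** The arcsine effect size is h = 2·arcsin√p1 − 2·arcsin√p2, and n per arm = 2(z_alpha + z_beta)²/h².
- At 21% vs 10%: h = 0.952 − 0.644 = 0.309. Two-sided n = 2(1.960 + 0.842)²/0.3086² = 164.9. One-sided n = 2(1.645 + 0.842)²/0.3086² = 129.9. The stated 157 and 124 do not follow from these rates.
- At 21.3% vs 10% (relative risk 2.13, the unrounded mean of the quoted 2.14, 2.05 and 2.20): h = 0.316, and n = 157.3 and 123.9. This matches the stated sizes, so the unrounded rate was probably used.
- Inflation: 314/0.75 = 419 and 248/0.75 = 331, as stated.

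**3. False claim of benefit.** Under no effect, a two-sided .05 test rejects in the favourable direction with probability .05/2 = 2.5%. A one-sided .05 test does so with probability 5%, a factor of 2. The two rules disagree exactly when the effect is favourable and the two-sided p lies between .05 and .10.

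**4. Two-sided power if only the one-sided size is recruited.**

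| Loss | AM, 208 recruited (d = 0.40) | SC, 331 recruited (21% vs 10%) |
|---|---|---|
| 25% | 78 per arm: 69.9% | 124 per arm: 68.1% |
| 10% | about 94 per arm: 78% | about 149 per arm: 76% |
| 0% | 104 per arm: 81.9% | 165.5 per arm: 80.1% |

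At 21.3% vs 10%, the SC figure for 124 per arm is 70.1%. The SC range at the planned loss is therefore 68–70%.

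**5. Power of each size under its own test.** AM: 99 per arm two-sided 80.0%; 78 per arm one-sided 80.0%. SC at 21% vs 10%: 157 per arm two-sided 78.1%; 124 per arm one-sided 78.4%. The SC shortfall is the same in both pairings, so it comes from the rounded quit rate and not from sidedness.

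**The case against.** The best case for the plan is that it is two-sided, with a one-sided alternative shown for information. For AM, the stated intention attaches to 264, and 208 appears only in parentheses. In both trials the attrition arithmetic is written out for the two-sided size alone. One-sided testing is described as mentioned, not as planned. Sidedness is also often confirmed in a statistical analysis plan, and that document is not shown.

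Much of this stands. The two-sided size leads, clearly in AM and less clearly in SC, where the two totals are simply joined. But the one-sided size stays in the same sentence as an available target, a reason is offered for it, and nothing withdraws it. The gap is not just detail left for an analysis plan, because the protocol itself prints two targets.

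Three stronger readings are tempting, and the document does not support them:
- **That 5% significance and 80% power cannot both be claimed.** Each AM pairing delivers both (step 5). What differs is the error in the direction of benefit.
- **That the trials are planned at about 70% power.** The document ties each size to its own test. The 70% arises only if size and test are mismatched and the full 25% is lost, a figure that the AM text calls a maximum.
- **That the test will be picked once results are known.** The half-way review concerns the assumptions behind the power calculation, with drop-out as the example, and does not mention sidedness. The protocol leaves room for such a choice but does not propose it.

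**Conclusion.** The point holds in a limited form and should be fixed. The two-sided plan leads, but a one-sided 5% alternative is left open on the plausibility of benefit alone, and the sidedness of the primary test is not fixed anywhere in the document.

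The consequence that needs no further assumption is the doubled chance of a false claim of benefit, and with it an ambiguous reading of any favourable result with two-sided p between .05 and .10. The loss of power is conditional: it assumes recruitment to 208 or 331, a two-sided test, the planning effect sizes, and the attrition shown in step 4. The directional wording of the hypotheses is ordinary and does not select a one-sided test.

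**What to change.** In Sample size, and again in Statistical analyses, state that each primary hypothesis is tested two-sided at alpha = .05. Keep 264 (AM) and 419 (SC) as the only targets. Delete the one-sided sizes and the sentence that justifies them. Add that sidedness will not change at the half-way review or if recruitment falls short; in that case, report the precision achieved under the two-sided analysis.

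For SC, state that 157 per arm gives about 78% power for 21% vs 10%, and that 80% would need about 165 per arm.

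The cost is wording only, because both targets are already in the protocol. Restoring 80% power in SC at the rounded rates would be a separate decision: 2 × 165/0.75 = 440, which is 21 more participants than 419.

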### Conditions

#### MyCourse – Quit smoking and MyCourse – Moderate drinking

Both programs are online lifestyle interventions optimized for cancer survivors: MyCourse – Moderate Drinking (in Dutch: MijnKoers – Minderen met Drinken) and MyCourse – Quit Smoking (MijnKoers – Stoppen met Roken) (see Fig. 2). The interventions are developed and tailored in collaboration with the target population of cancer survivors in focus groups and interviews, and in collaboration with several experts on eHealth, smoking cessation, alcohol misuse and cancer survivors.

**Fig. 2 Fig2:**
[figure not shown]
Main page of new online intervention MyCourse – Quit Smoking (in Dutch)

#### Therapeutic approaches: CBT, ACT and MI

Both interventions are based on cognitive behavioural therapy (CBT), acceptance and commitment therapy (ACT) and motivational interviewing (MI) techniques.

CBT has been well-established as an effective therapeutic approach for treating excessive alcohol use and aiding in smoking cessation in web-based programs [25, 26, 44]. It aids participants in understanding connections between cognitions, context and behaviour and hands them skills to cope with cognitions and situations that elicit unwanted behaviour. MI techniques help participants identify their ambivalences towards quitting smoking or moderating alcohol use, and help solve them [45]. MI has demonstrated a modestly significant effect in efficacy studies on smoking cessation, (RR 1.27; 95% CI 1.14 to 1.42) [45] and excessive alcohol drinking (d 0.40; 95% CI 0.17 to 0.70) [46]. National CBT- and MI-based treatment protocols were used to shape this part of the interventions [47, 48].

ACT is an emerging theory-based treatment paradigm that has demonstrated feasibility and efficacy in SC treatment in several studies and in a variety of modalities (face-to-face, telephone-based or web-based) [42, 49–51]. Regarding AM, a pilot trial found ACT-based group therapy for alcohol disorder and comorbid affective disorder effective [52]. Including the treatment of other substance use disorders (i.e. opioids, amphetamines, polydrug use) ACT shows favourable efficacy compared to other active treatment conditions (e.g. CBT and 12-step programs) and sustains the effects for a longer follow-up period [52, 53]. Acceptance in ACT stands for allowing intense physical sensations, cognitions, and emotions which may trigger drinking (AM RCT) and smoking (SC RCT) to come and go, without trying to control them; commitment stands for keeping in mind what is important to individuals (values) in order to guide action plans (stopping smoking) [42]. Specifically, ACT focuses on identifying thoughts, feelings, and physical sensations that trigger the target behaviour [42]. Unlike traditional CBT, ACT does not teach methods to avoid or control these triggers, but it focuses on changing one’s relationship with them by allowing them to be present without acting on them [42, 49, 54].

#### Optimization for cancer survivors

Patients participated throughout the development process. This resulted in all exercises being written in such a way as to better suit the needs of the population of cancer survivors. Information on short-term benefits is placed more prominently within the informative texts. Positive reinforcement is emphasized and effectuated in multiple ways, including badges and verbal reinforcements within the exercises. Support from the participant’s own social network was deemed highly important in the focus groups, so several exercises include a feature that enables quick, easy and personalized updates by sending a direct email to a friend, partner or relative. In addition, information regarding alcohol/tobacco and cancer interactions is included in the intervention. Because cancer survivors constitute a generally older age group, design has been simplified as much as possible. Clear instructions are given on every page, always including a help button, sharp contrasts ease reading.

#### Intervention flow

Both interventions are accessible through PC, tablet/iPad and smartphone. Length of the two interventions is equal. Participants are advised to use the intervention for 4 weeks after their set quit/moderation date, but they are free to quit whenever they want. After 4 weeks participants evaluate their goal achievement in the intervention. After this short evaluation all intervention components will remain available for at least 12 months. Table 1 shows descriptions of the main intervention elements, an overview of movement through these elements is shown in Fig. 3.

**Table 1 Tab1:** Main elements within new online interventions MyCourse – Quit Smoking and MyCourse – Moderate Drinking

Main elements	Description
Goal setting	Participants set a quit plan (SC and AM RCT) or moderation plan (only AM RCT) including a quit date
Goal monitoring	Every day participants monitor their drinking or smoking behaviour, mood, cognitions, and contextual cues which have led them to drink or smoke. Feedback is provided in a personalized graph
Exercises based on CBT and ACT	Exercises help identify high risk situations for excessive drinking/smoking and self-management strategies.
	ACT-exercises help accept difficult feelings while keeping focused on the behaviour goal and help exercise self-compassion to prevent relapse
Psycho-education	Effect of alcohol/tobacco on cancer, cancer treatment and life after cancer
Reminders	Several automated email reminders to regularly log on, monitor behaviour and finish all exercises
Peer support platform	A moderated bulletin board, focused on sharing tips and experiences
Social support from social network	Semi-automated email functions throughout the program to send personalized, informing emails to a trusted person

**Fig. 3 Fig3:**
[figure not shown]
Structure of online interventions MyCourse – Quit Smoking (SC) and MyCourse – Moderate Drinking (AM) *Legend:* Mail icons demonstrate semi-automatized email options to participants’ own social network. * Moderation plan/moderation date is possible in AM only

At the first login, participants are prepared for action using motivational interviewing-based techniques. Advantages and disadvantages of drinking (in AM RCT) or smoking (in SC RCT) and moderation/quitting are assessed. Next, ACT’s core process of committed action is targeted by having users apply their core values guiding quitting towards a personalized quit plan. Only for AM RCT: If moderation is chosen as a goal, the maximum amount of alcohol consumed per day and per week is set. The participant is also asked to set a date to start working towards the new drinking (AM RCT) or smoking cessation (SC RCT) goals. The quit date is to be set within 1 week upon logging in for the first time.

The next stage is the behaviour change phase, based on CBT. Here, participants are asked to monitor their drinking (AM RCT) or smoking (SC RCT), their mood, their cognitions, and contextual cues which have led them to drink (AM RCT) or smoke (SC RCT). Based on the monitoring data they provide, feedback is generated in the form of a graph to show progress towards their goals at a glance. This monitoring screen is shown first upon subsequent logins. In line with ACT, participants also monitor whether they have acted on their values each day. This is phrased as having engaged in a positive activity, where participants can choose from the values they have selected when setting their Quit/Moderation plan.

A personalized dashboard shows the different intervention components. Exercises are provided to help participants gain better insight into their drinking behaviour, and ways to handle cravings and high risk situations. In the final stage, participants learn how to manage relapse, and how to maintain behaviour change. ACT’s core processes of acceptance (preparedness to experience feelings or sensations), being present (staying connected with the here-and-now), cognitive reflection (watching the process of thinking), and self-as-context (awareness of the difference between one’s self and one’s thoughts) are targeted through a series of exercises designed to enhance these skills. Participants are invited to use these skills when they have urges, experience withdrawal symptoms or lapses [42].

On the peer support platform participants can provide and receive support from other participants during the intervention. Additionally they are encouraged to seek support from their own social network. Throughout the program, participants have the ability to share some of their answers with their partner or someone else who provides them support via semi-automatized emails. For example, they can share their quit plan or their high risk situations, thus helping their supportive social network in helping them by providing them with key information.

At any time, participants have quick access to an overview of their quit plan and finished exercises. To enhance adherence, emailed reminders are sent regularly after the participant has not logged in for several days, has not registered their drinking or smoking behaviour, or has not completed all exercises.

Throughout the interventions a sea faring ship is used as a metaphor. This is a means to help participants understand and experience the gist of ACT principles and foster continuity throughout the different intervention elements. Metaphors are used in ACT to loosen the grip of our cognitive thoughts on our feeling of self and on our behaviour. Using metaphors can circumvent the inclination to verbally protest against, for example, the exercise that explains how trying to exert control all the time will most likely not benefit you [55].

### Control conditions

The two control-condition interventions provide plain information on risks of alcohol (AM RCT) or smoking (SC RCT) in general and information specifically relevant for cancer survivors. Tips on how to reduce or quit alcohol use or quit smoking are also provided, but do not include the interactive elements that are part of the self-help interventions. Participants in the control groups can access the information page as often as they want by logging in on the website. However, the information on the information pages is static, does not change over time, and is not tailored to the individual participant. After completion of the study, 12 months post-randomisation, these participants are also provided with access to the self-help interventions. All participants are free to seek additional support if needed, use of additional support will be assessed in follow-up measures.

### Outcome measures

An overview of all measures and their measuring points is given in Table 2.

**Table 2 Tab2:** Schematic representation of outcome measures and measurement waves

Assessments (number of items)	baseline (t_0_)	3-months post-randomisation (t_1_)	6-months post-randomisation (t_2_)*	12-months post-randomisation (t_3_)
AAQ-II (7)	x	x	x	x
AUDIT (10)	x		x	
Knowledge questionnaire (12)	x	x	x	
BSI-18 (22)	x		x	
EQ-5D (5 + 1)	x	x	x	x
Fagerstrom Test for Nicotine Dependence (6)	x	x	x	x
MCSDS (13)	x			
OCDS^1^ (5)	x^1^	x^1^	x^1^	
Perceived partner support (1)	x	x	x	x
Self-efficacy measure (3)	x	x	x	x
SF36 (36)	x	x^a^	x	x^a^
Socio-demographics (24)	x			
TiC-P (31)	x	x	x	x
Timeline-Follow-Back (TLFB) for alcohol consumption (7)	x	x	x	x
Timeline-Follow-Back (TLFB) for tobacco consumption (7)	x	x	x	x
QSU-brief^2^ (10)	x^2^	x^2^	x^2^	
ZUF-8 (8)		x		

^1^= only applied in the AM RCT. ^2^ = only applied in the SC RCT. ^a^ = only 11 items from the SF36 will be administered at 3 and 12 months post-randomisation (necessary to apply the Brazier algorithm). * Primary endpoint for both the AM and SC RCT

### Primary measures

#### Alcohol and tobacco use

Main study parameters are Timeline Follow-Back (TLFB) reports on alcohol use (number of standard drinks) in the 7 days prior to the 6-month post-randomisation measurement wave (AM RCT) [56] and tobacco abstinence measured by TLFB reports on tobacco use (number of cigarettes) in the 7 days prior to the 6-month post-randomisation measurement wave (SC RCT). TLFB reports yield information on frequency as well as patterns of substance use behaviour [57, 58]. Outcomes from online administrated TLFB reports are consistent with face-to-face or telephone administrated TLFB reports [57, 59]. An additional question is sent in the SC RCT about tobacco use in the 14 days prior to 4 weeks after the set quit date, to comply with the Russell Standard and thus make the study better comparable to international smoking cessation studies [60].

### Secondary measures

#### Alcohol and nicotine dependence

Secondary measures include alcohol (AM RCT) or nicotine dependence (SC RCT) as measured by, respectively, the Alcohol Use Disorders Identification Test (AUDIT) [61] and Fagerstrom Test for Nicotine Dependence (FTND) [62]. AUDIT is a 10-item questionnaire on patterns of alcohol use and problems experienced due to alcohol use, to distinguish low-risk from high-risk drinkers. The AUDIT has been validated in 6 countries [61]. FTND is a 6-item questionnaire which has been shown to reliably assess nicotine dependence in a Dutch sample [63].

